## Materials and methods

### 1. Study settings

Intervention and comparison districts will be purposively selected from Dar es Salaam & Dodoma and Tanga & Mwanza Regions respectively with a view to minimizing contamination between intervention and comparison arms. In each region, the study area will include 20 health facilities, i.e., 10 health facilities from each district council. Health facility surveys will be conducted at baseline and end line in both the intervention and comparison areas, whereas the data use intervention will reach only the intervention district councils (two districts each in Dar es Salaam (Temeke and Kinondoni) and Dodoma (Dodoma City Council & Chamwino). The intervention districts will also be followed up at 6 months to measure the implementation outcomes and their determinants. To contextualize the settings of this study, we describe the study sites and the program.

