#### 2) Understand the initial (baseline) situation of data use in the study settings in relation to decision making and comprehensive (council or health facility) planning

To understand the baseline situation, the four councils implementing the data use initiative will be matched equally with comparable councils where the data use interventions will not be implemented. Stratified sampling (to distinguish the level of facilities) will be used in these four councils to select a representative sample of facilities to be observed for one year after the project is implemented. This step combines quantitative and qualitative methodologies to evaluate the current state of data use in the recipient health facilities.

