To assess the extent of adoption of the data use initiativesTo determine number or proportion of beneficiaries reached by the data use initiativeTo assess the fidelity to data use initiative protocol and SOPsTo assess acceptability of the data use initiative by primary beneficiaries and other stakeholdersTo assess sustainability of the data use initiative in the intervened primary health facilitiesTo determine the implementation challenges and success of the data use initiativesUnderstand the effects of the data use initiative on health system and patient outcomes

To understand the effects of the data use initiative, we will collect data at baseline and end line in order to allow two points measures of the outcome data. In this step, to assess compliance to national and international quality standards, the study team will rely both on the analysis of the routine health information system (at the facility level and district level) and information collected from respondents. Specific research questions include, i) has the quality of primary health facility data improved following implementation of the initiative? ii) What factors have contributed to the observed changes?

Specific objectives:-

Assess the effect/impact of data use initiative on beneficiaries’ capabilities (knowledge, and skills to analyze and interpret data)To evaluate the impact/effect of data use initiative on the quality of data collected in the primary health facilitiesTo determine the impact/effect of the initiative on the use of data for decision making and planningTo evaluate the effect of data use initiative on the performance of primary health facilities in terms of quality of delivered health services (availability drugs, medical supplies and equipment) and client’s satisfaction with the services.

*Study component 1*: *Measuring effects of the data use initiative*. This component aims at establishing the effects of data use initiatives on quality of care and selected health outcomes. To establish and control the counterfactual, data will be collected in the intervention and control councils. This component comprises collection of quantitative and qualitative data at two points (baseline and end line) covering a period of one year.

*Sampling and sample sizes*. This component will collect information from health facility documents , health care workers, and patients. The samples and sample sizes for this quantitative component are as follows

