We will collect health facility level data to assess the overall situation of quality of care from a total of 80 health facilities (40 from intervention health facilities & 40 from control health facilities).From each of the selected health facilities we will collect quantitative data from at least five participants (the chairperson of the health facility governing committee, in charge of the health facility, data focal person , in charge of RMNCAH services and in charge of outpatient services) making a total of 400 participants. This sample is adequate to conduct robust inferential analyses related to the effects of the data use initiative. Moreover, taking p = 50% and applying Cochrane formula while also accounting for refusals and the fact that some health facilities (especially the dispensaries) may not all the five staff, an addition of 10% to the minimum sample will be added to reach 440 participants.Also, from the selected facilities exiting patients will be systematically selected after gender stratification following medical consultations. The exit interview with Client/patients will be approached after they have received the services and are ready to go home. Respondents eligible for interview include all exiting patients or relatives of patients (aged above 18 years). They will be sampled to ensure equal numbers of men and women are captured. The sample is calculated using the Cochran formula (1977) [32]; by taking 50% as a proportion of patients’ perception on quality of primary health care services) and a power of 80% allowing for an estimated error margin of 5%, the sample size obtained was 384 patients. To account for refusals, an additional 10% of the sample will be added (n = 38), making a total of 422 patients.

The qualitative samples and sample sizes for this component are as follows:

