	3) To determine the impact/effect of the initiative on the use of data for decision making and planning		Documents, participants (health facility managers, health care workers, district managers/ CHMT members) and members of Health facility governing committees	Document review checklist, structured questionnaire, semi structured interview guides for in-depth interview and FGD
	4) To evaluate the effect of data use initiative on the performance of primary health facilities in terms of quality of delivered health services (availability drugs, medical supplies and equipment) and client’s satisfaction with the services.	availability of health system inputs, health system outcomes (responsiveness, quality of care and utilization of services) and client satisfaction	Documents, participants (health facility managers, health care workers, district managers/CHMT members) and members of Health facility governing committees	Document review checklist, structured questionnaire, Semi structured interview guides for in-depth interview
	5) To evaluate the effect of data use initiative health outcomes	Patient pathways, patient outcomes	Documents, participants (health facility managers, health care workers, district managers/CHMT members) and members of Health facility governing committees	DHIS extraction form, Document review checklist, structured questionnaire, semi structured interview guides for in-depth interview
	6) To determine the factors influencing the observed change in outcomes	Contextual factors	Documents, participants (health facility managers, health care workers, district managers/ CHMT members) and members of Health facility governing committees	Document review checklist, Semi structured interview guides for in-depth interview

The questionnaire for health workers will capture information related to socio-demographics, general knowledge on data use initiative, acceptability of the initiative to health workers, fidelity of implementation, sustainability of data use initiative and moderating factors. The questions in this tool will either be multiple choice, yes/no or Likert scale.

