3	Structured questionnaire	Health facility level	Face to face (guided), in ODK	Health care workers (N = 440), exit patients (N = 422)	Health care workers (N = 200)	Descriptive statistics (mean, standard deviation), Cross tabulation to compare groups’ performance Regression analysis for checking statistical significances among and between the participants Paired sample t test for comparing means between the baseline and end-line surveys
4	DHS2 extraction form	Health facility level / District level	electronic records	Health facilities (N = 40), Districts (N = 4)		Descriptive statistics on frequency, mean and standard deviation, Cross tabulation to compare performance of health facilities/ districts, Paired sample t-test for comparing means between the baseline and end-line surveys

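### Table 2 assigns a paired t-test to a row that includes exit patients, but the sampling yields two separate cross-sections of patients with no respondent-level pairs

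*Protocol article*

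**What the plan says.** Table 2, row 3 (structured questionnaire), lists the respondents for effects measurement as "Health care workers (N = 440), exit patients (N = 422"). One list of techniques serves both groups: descriptive statistics, cross tabulation, regression, and a "Paired sample t test for comparing means between the baseline and end-line surveys". Only the paired test is tied explicitly to the baseline versus end-line contrast, and no exception is made for exit patients.

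Under Study component 1, Sampling and sample sizes, "exiting patients will be systematically selected after gender stratification following medical consultations", and they "will be approached after they have received the services and are ready to go home". The respondent may be the patient or a relative. Section 1 (Study settings) says "Health facility surveys will be conducted at baseline and end line in both the intervention and comparison areas", and Study component 1 places data collection "at two points (baseline and end line) covering a period of one year". The article describes no patient cohort, re-contact or linkage between rounds.

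Facilities do carry over: the section on the baseline situation plans to "select a representative sample of facilities to be observed for one year after the project is implemented". Health-worker respondents under Study component 1 are defined by five named posts per facility.

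**The concern.** A paired t-test works on within-pair differences, so it needs a real link between each baseline and each end-line observation. The article's own sampling provides no such link for exit patients. An analyst following Table 2 literally would have to make pairs up, for example by row order. The p-value would then depend on how the file happens to be sorted. The test would also treat respondents as independent although they are grouped in facilities.

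The exit interview captures patients' perceptions of quality, and client satisfaction is part of one of the effectiveness objectives. The mismatch therefore affects the before-and-after test for a stated outcome.

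**Working it through.** **1. The plan's own figures.** The Cochran formula n = z²p(1−p)/d² with z = 1.96 (95% confidence is assumed, as the article does not state it), p = 0.5 and d = 0.05 gives 384.1. Then 384 × 1.10 = 422.4, so 384 and 422 reproduce. For workers, 80 × 5 × 1.10 = 440, which also reproduces. These figures count individuals and contain nothing about pairs.

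**2. The table against the sampling.**
- Row 3 counts individuals (440 and 422) and names a paired test.
- Row 4 (DHIS2 extraction) names the same test but counts facilities and districts. Those units are observed in both periods, so pairing is natural there.
- Exit patients are selected on leaving a consultation, at rounds covering one year. Respondent-level pairs guaranteed by this design: 0 of 422. The article does not say in words that the end-line patients are different people; this is inferred from the sampling.
- If 422 is the number per round over both arms (an assumption), there are 422/80 ≈ 5.3 patients per facility per round.

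**3. What pairing individuals does.** Two independent cross-sections were simulated with no true change: 80 facilities, 5 respondents each, a normally distributed score and 2,000 repetitions per setting. The article gives neither the facility intraclass correlation (ICC) nor the stability of facility effects between rounds (s, from 0 = unrelated to 1 = identical), so both were varied. Rejection rates at nominal 5%:

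| ICC | s | Paired, arbitrary | Paired by order within facility | Unpaired t-test | Paired facility means |
|---|---|---|---|---|---|
| 0 | 0 | 5.3% | 5.2% | 5.3% | 5.0% |
| 0.05 | 0 | 6.9% | 6.9% | 7.0% | 5.7% |
| 0.1 | 0 | 9.4% | 9.5% | 9.8% | 5.3% |
| 0.2 | 0 | 13.7% | 13.6% | 13.5% | 4.6% |
| 0.2 | 0.5 | 8.0% | 9.4% | 7.8% | 4.5% |
| 0.2 | 1 | 3.0% | 4.8% | 2.8% | 5.2% |

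**4. Check by formula.** With m respondents per facility, the true variance of the mean difference divided by the variance assumed under arbitrary pairing is 1 − ICC + m × ICC × (1 − s).
- For m = 5, ICC = 0.2, s = 0 this is 0.8 + 1.0 = 1.8. The real rejection rate is 2[1 − Φ(1.96/√1.8)] = 2[1 − Φ(1.461)] ≈ 14.4%, against 13.7% simulated.
- For s = 1 it is 0.8, giving 2[1 − Φ(1.96/√0.8)] = 2[1 − Φ(2.191)] ≈ 2.8%, against 3.0% simulated.

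**5. Reading.** Arbitrary pairing and the unpaired test behave alike, so the departure from 5% comes from facility clustering. Pairing at facility level, where real pairs exist, holds the level.

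**The case against.** The strongest reply is that row 3 pools two respondent groups in one cell with several techniques and does not say which applies to whom. Regression and cross tabulation are listed too, so exit patients are not left without a usable method. The same facilities are followed, and workers are defined by post, so a paired test by facility or by post could be run. Arbitrary pairing also added no type I error over an unpaired t-test.

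Much of this stands, and it rules out several stronger readings:
- A reader might infer that the paired test as such cannot validly be run. That is too broad. The defect is respondent-level pairing of exit patients.
- A reader might infer that the test is assigned to yes/no and Likert items, because "The questions in this tool will either be multiple choice, yes/no or Likert scale". That sentence describes the health-worker questionnaire of the process evaluation, not the exit interview. Row 3 limits the test to means, and section 5 sends categorical variables to chi-square or Fisher's exact test.
- A reader might infer that staff turnover would remove many worker pairs and bias the result towards those who stay. The documents give no turnover rate and do not establish a direction of bias. The absence of a described person ID is not evidence either, since the tools are in a supplementary file that is not shown.

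One part of the reply does not stand. The regression in row 3 has a different stated purpose (significance among and between participants) and does not withdraw the paired test. Nor does the table say that facility means are the paired unit; the numbers beside the test are individuals.

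**Conclusion.** Wrong as written for exit patients; should-fix. The article names a specific test that does not match its own sampling, so this is not detail that an article would normally leave to a fuller plan. The conclusion rests on reading the two exit-interview rounds as separate cross-sections, which follows from how patients are selected.

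On size: no patient pairs are guaranteed by the design. Over ICC 0 to 0.2 and facility stability 0 to 1, all assumed, a respondent-level test rejects a true null about 3% to 14% of the time. It would be wrong to conclude that pairing itself causes that inflation, because an unpaired t-test shares it. What pairing individuals adds is a p-value that depends on file order, with no gain in validity. For health workers the plan is not shown to be wrong; it leaves open whether person, post or facility is the unit.

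**What to change.** In Table 2, row 3:
- **Exit patients.** Remove the respondent-level paired t-test. Analyse the two rounds as repeated cross-sections with a regression containing arm, period and their interaction, plus a facility random effect. Alternatively, take the change in mean for each of the 80 facilities and compare these changes between the 40 intervention and 40 control facilities.
- **Health workers.** Use the same model on all respondents in both rounds, adding a person effect only where a study ID links the same individual, or pair at facility level. State which unit is used.

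For patients the cost is a change of wording and slightly more analysis work. For workers, a study ID field in the electronic questionnaire is needed only if persons are to be linked, and it must then be in place at baseline. Sample sizes and fieldwork are otherwise unchanged.

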**Methods:**

We will conduct a hybrid type 2 effectiveness-implementation study employing a mixed method controlled before and after design to measure the effects of data use interventions while simultaneously understanding the implementation of those initiatives. The controlled before and after entails measurement of the effects of the interventions at baseline and end line in a matched intervention and control health facilities using structured questionnaire to health workers (n = 440) and existing patients (n = 422) while also extracting selected health outcome variable from routine data in all participating health facilities (n = 80). The mixed methods component entails measuring the implementation outcomes (adoption, acceptability, fidelity and maintenance) and their moderators entails the integration of both quantitative and qualitative data collection, analysis, and interpretation (i.e. mixed methods) approach by using a structured questionnaire to implementers (health workers and managers) (n = 400). Experiential dimensions of implementation processes and moderators will be explored using qualitative interviews. Guided by implementation research theories and frameworks, a theory of change (TOC) is developed first to guide the evaluation of implementation processes and effects of the interventions. Descriptive and inferential statistics will be employed to analyze quantitative data whereas thematic analysis approach will be employed for qualitative data.

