### 2. Study design

This study will adopt an effectiveness-implementation type-2 hybrid design [22] to evaluate the effectiveness of the data use initiatives in improving quality of health service delivery and health outcomes while simultaneously understanding the implementation of the initiatives. Since the data use initiative is implemented in twenty health facilities of two regions, we plan to carry out a before and after controlled design to estimate the combined effects of the data use initiatives in the intervention sites and matched control regions. Simultaneously we plan to assess the implementation processes of the initiatives and this entails the integration of both quantitative and qualitative data collection, analysis, and interpretation methods (i.e. mixed methods) to understand the implementation processes and the influencing factors.

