*Sampling and sample sizes*. Our sample for measuring the implementation process (process evaluation) will include implementers of the data use initiative at the council and health facility level. The participants will be implementing partners, health care mangers and health facility governing committee members (CHMT, HFGCs, health facility-in charges and frontline health workers). The fact that all CHMT members are guardians of data use at the council and its respective health facilities, they will all be included in the study (census) thus making a total of 60 CHMT members i.e., at least 15 members from each of the participating council. At least two members of HFGCs will be recruited in the study making a total of 80 HFGC members. A consecutive sample of health care workers from the participating health facilities with a maximum of five participants based on the assumption that the selected facilities should have a minimum of five health care workers, i.e., a total of 200 health workers will be recruited in the study. In addition, routine health facility files and documents will be read and summarized to fit the study context.

*Data collection tools and procedures*. The domains for the implementation process evaluation are reach, adoption, fidelity of implementation, acceptability and sustainability. Data will be collected from the following types of participants and documents; implementing partners, health care managers and health facility governing committee members (CHMT, HFGCs, health facility -in charges and frontline health workers) and health facility documents. Table 1 provides the details on the set of tools and their alignment to objectives and sources of data. In line with our mixed methods design, quantitative data will be gathered using; structured questionnaires, document review/ observation checklists, and semi-structured in-depth interviews (IDIs).

**Table 1 pone.0303552.t001:** The set of tools and their alignment to objectives and sources of data.

Study component	Objective	Domain/ Data required	Sources of data	Data collection tools
Development of a Theory of change	Develop a theory of change (TOC) for data use initiatives and document the process under which such a TOC is developed		Documents, participants (data use initiative designers and implementers)	Document review checklist, Semi structured interview guides for in-depth interview

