### 5. Analytical procedures

Descriptive analysis will be used to summarize data where by continuous data will be summarized using mean and standard deviation (SD) as well as medians and interquartile range. Dichotomous variables will be summarized using frequency and percentage. Chi-square test or fisher exact will be used to evaluate bivariate associations between categorical variables where by t-test will be used to estimate association in numeric variables and ascertain whether there mean different between categories. We will also use regression analysis.

Audio-recordings of in-depth interviews and focus group discussions will be transcribed verbatim in Kiswahili guided by a transcription guideline and translated to English. Transcription and translations will be done by the research team that conducted the respective IDIs. Codes will be grouped into categories, sub-themes and themes. Thematic analysis will be used to analyze qualitative data using ATLAS.ti 8 software. Table 2 provides details on data collection tools, administration, sample size and analytical techniques.

**Table 2 pone.0303552.t002:** Data collection tools, administration, sample size and analytical techniques.

S/N	Data collection tool	Level (s) of administration	Method of administration	Sample size (effects measurement)	Sample size (process evaluation)	Analytical techniques
1	Document review checklist	CHMT and Health facility level	physical and e-records, in ODK	Health facilities (N = 40), Districts (N = 4)	Health facilities (N = 20), Districts (N = 2)	Descriptive statistics on frequency, mean and standard deviation, Cross tabulation to compare performance of the participants
2	Semi structured interview guides for in-depth interview	All levels (national, regional, district, health facility, community representatives)	face to face	Patients, dispensary (N = 32), Patients, health center (N = 32), Health care workers, Dispensary (N = 16), Health care workers Health centers (N = 16),	Health facility governing committee members (N = 80), CHMT members (N = 60), RHMT members (N = 4), implementing partners (N = 4)	Thematic analysis will be used to analyze qualitative data using ATLAS.ti 8 software

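### Table 2, section 2 and the abstract give facility, district and implementer numbers that conflict with the 80-facility, eight-council design

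*Protocol article*

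**What the plan says.** **Design.** The abstract says that routine outcome data come from "all participating health facilities (n = 80". Section 1 states: "In each region, the study area will include 20 health facilities, i.e., 10 health facilities from each district council". With four regions and eight named councils, that is 80 facilities. The component 1 sampling text in section 4 collects facility data "from a total of 80 health facilities (40 from intervention health facilities & 40 from control health facilities".

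**Table 2 (section 5).** Rows 1 and 4 (document review and DHIS2 extraction) give "Health facilities (N = 40), Districts (N = 4" for effects measurement. Row 1 gives "Health facilities (N = 20), Districts (N = 2" for the process evaluation. Neither cell is labelled as per arm, per region or a subsample.

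**Section 2.** It gives as the reason for the design that "the data use initiative is implemented in twenty health facilities of two regions".

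**Implementers.** The abstract measures implementation outcomes "using a structured questionnaire to implementers (health workers and managers) (n = 400". Component 2 lists 60 CHMT members, 80 HFGC members and health workers, of whom "a total of 200 health workers will be recruited in the study". The first two groups are given as minimums per council and per facility. In Table 2, the process-evaluation questionnaire (row 3) goes to 200 health workers only. The 80 HFGC and 60 CHMT members appear in row 2, under in-depth interviews.

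**The concern.** Table 2 is where the article links each tool to its sample size and its analysis. DHIS2 extraction is the stated source of the health outcomes, and component 1 relies on data from both arms for its counterfactual. A count of 40 facilities and 4 districts happens to equal the intervention arm. In row 4 it stands beside a paired baseline-to-endline t-test, so a field team or analyst working from the table could extract one arm and compare before with after. The other literal reading, 40 facilities split over two arms, keeps the comparison with half the facilities.

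The twenty in section 2 leaves it unclear which facilities make up the intervention arm. The implementer figures leave it unclear who completes the questionnaire on adoption, acceptability, fidelity and maintenance, and so what denominator those results will have.

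**Working it through.** **1. Reproduce the design figure.**
- Section 1: 4 regions × 20 = 80 facilities; equivalently 8 councils × 10 = 80.
- Intervention arm: 4 councils × 10 = 40, or 2 regions × 20 = 40.
- Section 4: 40 + 40 = 80. The abstract, section 1 and section 4 agree.

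**2. Compare with Table 2.**

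| Item | Abstract and sections 1 and 4 | Table 2 | Ratio |
|---|---|---|---|
| Effects, rows 1 and 4 | 80 facilities / 8 districts | 40 / 4 | 0.5 |
| Process, row 1 | 40 / 4 (intervention councils) | 20 / 2 | 0.5 |

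**3. Test Table 2 against its own other rows.** The per-unit rates are those in section 4.

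Effects column:
- Health workers: 80 × 5 = 400, and 400 × 1.10 = 440, as tabulated. With 40 facilities: 40 × 5 × 1.10 = 220.
- Patient interviews: 8 × 8 councils = 64, as tabulated (32 + 32). With 4 councils: 32.
- Worker interviews: 4 × 8 councils = 32, as tabulated (16 + 16). With 4 councils: 16.

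Process column:
- CHMT members: 15 × 4 councils = 60, as tabulated. With 2 councils: 30.
- HFGC members: 2 × 40 facilities = 80, as tabulated. With 20 facilities: 40.
- Health workers: 5 × 40 facilities = 200, as tabulated. With 20 facilities: 100. Since five per facility is a maximum, 200 workers cannot come from 20 facilities.

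So the table's respondent counts fit 80/8 and 40/4, not 40/4 and 20/2.

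**4. Section 2.** Twenty facilities in two regions, against 2 × 20 = 40 from section 1 and 40 intervention facilities in section 4.

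**5. Implementers.**
- Component 2: 60 + 80 + 200 = 340. Adding the 4 RHMT members and 4 implementing partners of Table 2 gives 348.
- A 10% allowance does not close the gap: 340 × 1.10 = 374, not 400.
- Process questionnaire in Table 2: 200.
- 400 equals the component 1 base of 80 × 5, so it may have been carried over. That is an inference; the article does not say so.

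**6. Size under the 20 v 20 reading.** The standard error of a difference between arms in a facility-level mean is proportional to √(2/n), with n facilities per arm. The ratio is √(2/20) ÷ √(2/40) = √2 = 1.41. At 80% power and two-sided 5%, the detectable difference is (1.96 + 0.84) × √(2/n): 0.89 SD with 20 per arm against 0.63 SD with 40. This treats facilities as independent and ignores council clustering.

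**The case against.** The best defence is that the prose settles the design. The abstract names all 80 facilities for routine data, section 1 surveys both areas, and section 4 gives 40 + 40. Faulty table cells are then likelier than a plan to drop the controls. That stands, and it limits the consequence: a reader might infer from Table 2 that the control arm is excluded from the outcome data, but the article does not plan this. It would follow only if the table were taken literally over the text.

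A second defence is that 40/4 is a per-arm count. The table does not say so, and the worker and interview numbers in the same column cover both arms. A per-arm reading also cannot explain 20/2, since the process component runs in the intervention arm only.

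Third, component 2 never states how many facilities have their documents reviewed, and 20/2 matches one region. A declared subsample would therefore be legitimate. This also stands: the conflict in that cell is inferred from the four intervention councils and the other process counts, and the table declares no subset.

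Two further inferences should be resisted. One is that, with twenty facilities served, half the intervention arm is unexposed, the effect is halved and four times the sample is needed. That assumes no effect in facilities without facility-level support. The initiative also acts at council level, so such facilities could still benefit, and a dropped reference to each region is a simpler explanation of the twenty. The other is that 200 is a rival total. It is the health-worker subset, on which component 2 and Table 2 agree.

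**Conclusion.** The contradictions are real and should be resolved before the table is used. Table 2 rows 1 and 4 give half the design's facilities and districts for effects measurement. Row 1 gives half of those in the intervention councils for process, with no subset declared. Section 2 gives twenty facilities where sections 1 and 4 imply 40. The abstract's questionnaire number of 400 matches neither the 340 participants of component 2 nor the 200 questionnaire respondents of Table 2.

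The cost depends on whether Table 2 is followed. If it is, either no controlled estimate exists for the DHIS2 and document outcomes, or their standard errors are about 1.41 times larger. The factor belongs to the 20 v 20 reading and to outcomes collected under rows 1 and 4 only; it does not extend to the facility assessment, which section 4 places in all 80 facilities. No dilution of the effect can be quantified, because the article does not say which facilities receive what level of support.

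**What to change.** - **Table 2.** Set effects measurement in rows 1 and 4 to 80 facilities and 8 districts, and process evaluation in row 1 to 40 facilities and 4 districts. If a subset is intended, say so and state how it is chosen.
- **Section 2.** Correct to 40 facilities, 20 per region. If only twenty receive facility-level support, state that and restate the intervention arm and its numbers.
- **Implementers.** State which implementers complete the process questionnaire, and use one figure in the abstract, component 2 and Table 2: 200 if health workers only, about 340 if HFGC and CHMT members are included. Simply replacing 400 by 340 in the abstract would create a new conflict, because Table 2 places 80 + 60 = 140 of those 340 under in-depth interviews.

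The cost is a few table cells, one design sentence and one abstract figure, with matching wording in component 2. No additional data are needed if 80 facilities are already planned.
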